## Abstract

**Background:**

Bipolar disorder is a severe mental illness with serious consequences for daily living of patients and their caregivers. Care as usual primarily consists of pharmacotherapy and supportive treatment. However, a substantial number of patients show a suboptimal response to treatment and still suffer from frequent episodes, persistent interepisodic symptoms and poor social functioning. Both psychiatric and somatic comorbid disorders are frequent, especially personality disorders, substance abuse, cardiovascular diseases and diabetes. Multidisciplinary collaboration of professionals is needed to combine all expertise in order to achieve high-quality integrated treatment. 'Collaborative Care' is a treatment method that could meet these needs. Several studies have shown promising effects of these integrated treatment programs for patients with bipolar disorder. In this article we describe a research protocol concerning a study on the effects of Collaborative Care for patients with bipolar disorder in the Netherlands.

**Methods/design:**

The study concerns a two-armed cluster randomised clinical trial to evaluate the effectiveness of Collaborative Care (CC) in comparison with Care as usual (CAU) in outpatient clinics for bipolar disorder or mood disorders in general. Collaborative Care includes individually tailored interventions, aimed at personal goals set by the patient. The patient, his caregiver, the nurse and the psychiatrist all are part of the Collaborative Care team. Elements of the program are: contracting and shared decision making; psycho education; problem solving treatment; systematic relapse prevention; monitoring of outcomes and pharmacotherapy. Nurses coordinate the program. Nurses and psychiatrists in the intervention group will be trained in the intervention. The effects will be measured at baseline, 6 months and 12 months. Primary outcomes are psychosocial functioning, psychiatric symptoms, and quality of life. Caregiver outcomes are burden and satisfaction with care.

**Discussion:**

Several ways to enhance the quality of this study are described, as well as some limitations caused by the complexities of naturalistic treatment settings where not all influencing factors on an intervention and the outcomes can be controlled.

**Trial Registration:**

The Netherlands Trial Registry, NTR2600.

## Background

Bipolar disorder is a severe mental illness with an estimated lifetime prevalence of 1.5 to 2%[1]. It is characterized by recurrent episodes of extreme mood changes. Several studies [2-4] show that on average patients suffer from manic, depressive, hypomanic or mixed symptoms for about half of the time despite treatment. Even during so-called euthymic periods, i.e. when they are formally not in a mood episode, many patients suffer from subsyndromal symptoms that negatively influence their quality of life [5]. Informal caregivers also suffer a substantial burden by the illness, not only during episodes [6,7].

Treatment of bipolar disorders in the Netherlands primarily consists of pharmacotherapy, supportive treatment, and psycho education, sometimes combined with improvement of self-management skills or psychotherapy. Many patients respond well to this treatment and may stabilize for longer periods. However, a substantial number of patients do not respond adequately to these treatment efforts. They suffer from frequent episodes, persisting symptoms, cognitive problems, limited social support and poor social functioning. Comorbid psychiatric disorders, such as personality disorders and substance abuse, are common, as are somatic disorders i.e. cardiovascular disease, partly associated with prolonged use of maintenance medication [8,9].

Multidisciplinary collaboration of professionals is needed to involve optimal specialist skills on all aspects of the disorder, and to properly combine all expertise in order to achieve an optimally integrated care [10]. The Dutch guideline for the treatment of bipolar disorders [11] recommends such an integrated treatment. The guideline advises that treatment be targeted at reducing symptoms, acceptance of the illness, promoting treatment adherence, stabilising social rhythm, recognising early signs and symptoms and take proper actions when these occur, diminishing social problems and maximising social participation. It is advised to actively engage caregivers or family members in this treatment. Although it is widely acknowledged that integrated treatment programs can be of great value for patients with bipolar disorder, research on the effectiveness of such programs for patients with a bipolar disorder is scarce.

Collaborative Care (CC) programs have been developed to integrate multidisciplinary care for complex disorders and to date, three research projects show promising results with bipolar patients. Bauer et al. [12,13] have implemented a CC model for patients with bipolar disorder and measured the effects in two randomised controlled trials. Patients participated in the Life Goals Program. The intervention consisted of improving patients' self-management skills through psycho education; supporting providers' decision making through simplified practice guidelines; and enhancing access to care and continuity of care. The care manager, a nurse or a social worker, provided actively outreaching care when a patient was at risk of losing contact with mental health workers. Each patient made a 'relapse prevention plan', aimed at the early recognition of relapses. The care manger contacted the patient at least every three months. The program also provides guidelines for specific pharmacotherapy. Bauer et al. [12,13] found significantly reduced number of weeks in manic episodes in the experimental group, although no significant effect was found on weeks depressed. Patients showed improved social functioning, quality of life and treatment satisfaction. Total costs were similar in both groups. The Life Goals Program was extended by Kilbourne et al. [14,15], to address the many medical comorbidities present in patients with bipolar disorders.

Simon et al. [16,17] have explored the effects of adding intensive nursing care to treatment of patients with bipolar disorder. This consisted of an emergency plan, monthly telephone calls in which symptoms were monitored, sharing of information between nurse and psychiatrist, and outreach interventions such as crisis intervention. Patients were given the choice of participation in the Life Goals Program, mentioned above. After receiving the intervention over a period of one or two years, patients in the experimental group showed significant less severe manic symptoms of shorter duration. Also in this study, there was no effect on depressive symptoms. Extra costs of this treatment were relatively low compared to the control group.

Suppes et al. [18] studied the effects of the Texas Medication Algorithm project in patients with bipolar disorder. This project aimed to develop and implement algorithms for pharmacotherapy for bipolar patients. Clinics implementing this guideline were compared in a RCT to clinics which did not use the guideline. In the experimental group, a coordinator was added to the care team. This coordinator provided psycho education to the patient and the family. He kept in contact with the patient, and assessed symptoms and side effects of medication prior to each consultation with the psychiatrist. The coordinator informed the psychiatrist about the results of these assessments. The aim was to achieve a higher efficiency of the psychiatric consultations. The results of the study show a significant improvement of psychiatric symptoms of patients in the intervention group in the first three months. During the next nine months, patients in the control group improved as well, but less than patients in the intervention group. Patients in the intervention group reported significant improvement of manic, but not depressive and psychotic symptoms.

It is striking that all three studies show improvement of manic but not depressive symptoms.

In the Netherlands, until now no studies have been performed on the effects of CC for patients with bipolar disorder. The current study will be the first to implement CC for patients with bipolar disorder, and moreover, to add a specific intervention to improve depression. Furthermore, CC appears to offer good possibilities to strengthen the position of the nurse in the care process for patients with a bipolar disorder, both at the organizational and content levels.

In this article we describe the study protocol for investigating the effectiveness of a CC program for patients with bipolar disorder. We set out the following three research questions to answer:

A What are the effects of a CC program, compared to Care as Usual (CAU), for patients with bipolar disorder, with regard to their psychosocial functioning, psychiatric symptoms, quality of life, attitudes towards medication, mastery, and satisfaction with care?

B What are the effects of a CC program, compared to CAU, for informal caregivers of patients with a bipolar disorder, with regard to the experienced burden and satisfaction with care?

C What is the cost effectiveness of a CC Program compared to CAU?

## Methods/design

### Design

A pragmatic two-armed cluster randomized controlled trial (RCT) will be carried out in mental health outpatient clinics in the Netherlands. A Collaborative Care program will be executed in the experimental condition, whereas the control condition will continue to deliver Care as Usual (CAU). CC will be performed by the CC-team, with mental health nurses in a coordinating role. Baseline measurements will be obtained at inclusion and follow-up measurements will take place at 6 months and 12 months. The primary outcome measures are psychosocial functioning, symptoms, and quality of life. Secondary outcome measures are mastery, attitude towards medication and satisfaction with care. Family members or friends of patients will be asked to fill in questionnaires regarding perceived burden and satisfaction with care.

### Study on Care as Usual

The level of CAU may vary considerably among the various outpatients clinics in the Netherlands, and there is a lack of clarity about the specific content of CAU for patients with bipolar disorder. However, there is more detailed knowledge available about care provided in some highly specialized centres for patients with bipolar disorder that may resemble CC. In the Netherlands, about 20.000 patients receive care for bipolar disorder but it is estimated that only 1500 patients receive this care in these specialized centres. Hence, about 18.500 patients receive CAU at a less specific level. Our presumption is that CC will differ considerably from CAU, which we expect to be mainly supportive and not systematically delivered. In order to increase our knowledge about the characteristics of CAU another study has started to describe current CAU for bipolar disorders in the Netherlands. In this study, psychiatrists and patients are being asked to describe the care actually delivered to patients with bipolar disorder, by means of questionnaires. These data will be used in the current study: (1) to objectively describe CAU; (2) to select sites (based on our inclusion criteria) that can be included in our CC-trial; and (3) to perform the matching of sites for the (cluster) randomization. Furthermore, if outpatient care teams are interested in participating in the CC-trial, we will interview two members of that team to investigate the nature and intensity of care currently delivered to patients with bipolar disorder. Clinics that currently have a level of CAU that does not already resemble CC can be considered for randomisation.

### Randomisation

In this trial we will use clustered randomisation with outpatient clinic teams as clusters. Randomisation will be performed as follows: the CAU-study as well as the interviews with team members provide us with insight in the nature and intensity of CAU at that site. This enables us to describe CAU more precisely and formulate criteria for inclusion. Sites that meet the criteria for CAU will be invited to join in the CC-trial. Teams will be matched for characteristics of care offered to bipolar patients, as well as organisational characteristics such as team composition or type of organisation. One team of every pair will be randomly assigned to the experimental condition, and the other to the control condition. Patients in both teams who meet the inclusion criteria will be asked to participate in the study.

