### Respondents

Patients who meet the following inclusion criteria will be included:

• diagnosis of bipolar disorder according to DSM- IV-TR [19];

• age 18-65 years.

Exclusion criteria:

• Acute phase of severe depression or mania (CGI-BP: degree of illness score 6 or score 7).

• A very stable course of illness (during the last year) that allows low intensity of treatment (2-4 consults with the psychiatrist per year suffice), to be judged by the treating psychiatrist.

• Insufficient command of the Dutch language.

• Not able or willing to give informed consent.

If the patient consents, a family member or friend will also be asked to participate in the study, according to the following inclusion criteria:

• The family member or friend is assigned by the patient.

• The family member or friend is 18 years or older.

• The family member or friend has a sufficient command of the Dutch language.

• The family member or friend is able and willing to give informed consent.

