### Blinding

Since the current study is a pragmatic intervention study, blinding of patients and professionals for care modality is not possible. However, blinding is performed in the procedure of randomisation and the statistical analysis. Furthermore, the research assistant who performs interviews by telephone to administer the Life Chart, will be blind to the condition of the respondent.

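### Patients appear to be approached after their team has been allocated, with a partly discretionary exclusion judged by an unblinded psychiatrist, so eligibility and consent can differ by arm

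*Protocol article*

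**What the plan says.** The unit of allocation is the team: "In this trial we will use clustered randomisation with outpatient clinic teams as clusters". The Randomisation section sets out its steps in order. Usual care is characterised, suitable sites are invited, teams are matched, and "One team of every pair will be randomly assigned to the experimental condition, and the other to the control condition". The next and last sentence is "Patients in both teams who meet the inclusion criteria will be asked to participate in the study". The Design section adds "Baseline measurements will be obtained at inclusion".

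Under Respondents, one exclusion is "A very stable course of illness (during the last year) that allows low intensity of treatment". It is tied to two to four psychiatrist consultations a year being enough, and it is "to be judged by the treating psychiatrist". Another exclusion is "Not able or willing to give informed consent". The acute-phase exclusion uses CGI-BP severity, which Table 1 lists as completed by the clinician.

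The Blinding section says "blinding of patients and professionals for care modality is not possible". The blinding it does provide covers the randomisation procedure, the statistical analysis and the Life Chart interviewer.

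**The concern.** Randomising teams makes the two sets of teams comparable on average. It makes the enrolled patients comparable only if enrolment does not depend on the arm. If eligibility is judged and consent sought once the allocation is known, two steps can work differently in the two arms.

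- **Eligibility.** A psychiatrist who knows whether the team will deliver CC decides whether a patient is too stable to be included.
- **Consent.** CC patients are asked to join a year-long active programme. Usual-care patients are asked mainly to complete measurements. Willingness to take part could plausibly differ.

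The caregiver sample would inherit any such difference, because each caregiver is chosen by an enrolled patient. At stake is whether a difference at 12 months reflects the programme or who was enrolled. Analysis cannot fully repair this afterwards.

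**Working it through.** **Step 1: order of events.** The Randomisation section says that it describes how randomisation will be carried out, and it puts the request to patients directly after the assignment of teams. No other section places identification or listing of patients before allocation. The Design sentence on baseline ties T0 to inclusion, not to allocation, so it neither confirms nor contradicts this order. The timing is an inference from the order of the steps.

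**Step 2: who decides, and what they know.**

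| Step | Decided by | Blind to arm? |
|---|---|---|
| Very stable course | Treating psychiatrist (Respondents) | No (Blinding) |
| Acute phase, CGI-BP 6 or 7 | Clinician rating (Respondents, Table 1) | No (Blinding) |
| Consent | Patient (Respondents) | No (Blinding) |

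**Step 3: do the existing safeguards reach these steps?**
- Blinding of the randomisation procedure protects the assignment of teams, not later enrolment within them.
- Blinding of the analysis and of the Life Chart interviewer acts after enrolment.
- Matching balances teams on care and organisation, not on which of their patients enter.
- The baseline score as covariate, and the comparability tests on demographic and clinical variables (Statistical analysis), reduce or reveal imbalance in what is measured. They do not remove differences in motivation, willingness or unmeasured prognosis.
- Intention to treat applies to patients already enrolled.
- The Discussion names three limitations: lack of blinding, the effect of assessments on the control group, and the inability to separate components. It treats expectation as something that acts during treatment, not at enrolment.

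**Step 4: scale (illustration only).** The plan's own starting figure reproduces: n per arm = 2 × (1.960 + 0.842)² / 0.5² = 62.8, rounded up to 63. Take 63 effective patients per arm and no true effect. Let b be an assumed residual difference between arms in SD units, after baseline adjustment, caused by enrolment.

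SE = √(2/63) = 0.178. Rejection rate = Φ(b/SE − 1.96) + Φ(−b/SE − 1.96).

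| Assumed b (SD) | b/SE | Two-sided rejection rate |
|---|---|---|
| 0.05 | 0.28 | 5.9% |
| 0.10 | 0.56 | 8.7% |
| 0.20 | 1.12 | 20% |
| 0.30 | 1.68 | 39% |

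One way to reach such values is through the stability exclusion. If the share of very stable patients differs between arms by 10 to 20 percentage points, and their outcome differs by 0.5 to 1.0 SD, the shift runs from 0.10 × 0.5 = 0.05 to 0.20 × 1.0 = 0.20 SD before any baseline adjustment. None of these inputs is in the documents. The tables show only that modest shifts would matter, not that they will occur.

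**The case against.** The strongest reply has four parts.

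- **The sequence is inferred.** The section gives no dates and does not say when allocation is disclosed to the teams. This stands, and it is why the point is worded as what appears to happen.
- **The text reads as asking every eligible patient.** A reader might infer that CC clinicians hand-pick likely responders. No section says that clinicians nominate patients, or who approaches them, so that stronger reading is not supported. What remains is narrower: who counts as eligible, and who consents, is settled by unblinded people.
- **The exclusion is not free-form.** It has a one-year look-back and a consultation frequency that can be compared with records. This stands in part, but whether that frequency is enough for a given patient is still a judgement.
- **A condensed article leaves screening lists, recruiters and logs to the full protocol.** This is fair, and their absence is not the finding. The finding rests on what the article does state: the order of steps, who decides on the exclusion and the lack of blinding.

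It is also fair that measured prognosis is well covered. The QBP-NL records illness history and current characteristics, and baseline comparability is examined. That limits the problem without reaching unmeasured differences.

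**Conclusion.** The concern holds in a limited form. Followed as written, the plan allows eligibility judgement and consent to differ by arm; no stated safeguard covers patient-level enrolment, and the risk is not acknowledged. The conclusion assumes that the order of steps in the Randomisation section is also the order in time, and that teams know their allocation when they judge eligibility.

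The size and direction of any bias cannot be determined from the documents. A reader might infer that a stated share of the planned d = 0.5 is at risk, or that the bias favours CC. Neither is supported: any such figure comes entirely from assumed inputs, and similar selection in both arms would partly cancel. This is an inexpensive improvement to make before recruitment, not evidence that the trial will be biased.

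**What to change.** Before a pair's allocation is disclosed to its teams:
1. Both teams screen their caseload and apply the existing stability exclusion. It looks back over the past year, so it does not need the allocation to be known.
2. The list of eligible patients in each team is fixed.

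After disclosure:
1. Everyone on the list is approached.
2. Only the existing acute-phase and consent criteria are re-checked.
3. Numbers listed, approached and consenting are reported by arm.
4. Selective recruitment is named among the limitations.

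**Cost.** Disclosure and CC training for a pair wait until both lists are fixed. Screening takes some clinician time, and acute-phase status can change, so it must be re-checked at consent. That re-check and consent itself remain unblinded; the counts by arm make selection there visible but do not prevent it. Moving consent and T0 ahead of disclosure would protect further, but it should be optional: training must still follow, which could open a gap between T0 and the start of CC while follow-up is counted from baseline. No eligibility criterion or treatment element changes.

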### Respondents

Patients who meet the following inclusion criteria will be included:

• diagnosis of bipolar disorder according to DSM- IV-TR [19];

• age 18-65 years.

Exclusion criteria:

• Acute phase of severe depression or mania (CGI-BP: degree of illness score 6 or score 7).

• A very stable course of illness (during the last year) that allows low intensity of treatment (2-4 consults with the psychiatrist per year suffice), to be judged by the treating psychiatrist.

• Insufficient command of the Dutch language.

• Not able or willing to give informed consent.

If the patient consents, a family member or friend will also be asked to participate in the study, according to the following inclusion criteria:

• The family member or friend is assigned by the patient.

• The family member or friend is 18 years or older.

• The family member or friend has a sufficient command of the Dutch language.

• The family member or friend is able and willing to give informed consent.

### Blinding

Since the current study is a pragmatic intervention study, blinding of patients and professionals for care modality is not possible. However, blinding is performed in the procedure of randomisation and the statistical analysis. Furthermore, the research assistant who performs interviews by telephone to administer the Life Chart, will be blind to the condition of the respondent.

### The intervention

CC will be recovery-oriented, meaning that it supports the personal process of the patient towards redefining and achieving his goals in life despite the disorder. It will consist of the following systematically delivered elements of treatment:

• The formation of a Collaborative Care team, including at least the patient, the nurse and the psychiatrist, were all decisions concerning treatment and care will be made, using shared decision making. If possible, a family member or friend will be engaged in the treatment and be part of the CC team. Teams meet every three months. Coordination of care and continuity of care is provided by the nurse.

• Contracting. Agreement on the most important problems to be worked on, and on which treatment is needed to help the patient achieve his personal goals, will be striven for. A treatment plan will be made, formulated as a contract, in which goals and treatment activities are recorded.

• Working with the treatment plan based on systematic care needs assessment, and that will focus specifically on recovery-oriented goals, defined by the patient. Systematic monitoring of outcomes.

• Psycho education [20,21]), provided as a course directed at a group of patients and caregivers.

• Problem Solving Treatment (PST) [22,23], delivered by the nurse.

• Mood charting by means of the Life Chart Method [24] and recognising early warning signs of relapse [25-27].

• Pharmacotherapy and somatic care, as usual. In addition, structured and continuous monitoring of the effects.

• If indicated, specialised PST will be delivered (1) to patients who remain depressed, aimed at increasing the amount of pleasant or fulfilling activities, and (2) to patients with wishes or care needs on the subject of participation in society, aimed at rehabilitation.

These interventions will be tailored to the individual needs of the patient.

In the CC trial, CC will be implemented in the experimental teams by the use of the Replicating Effective Programs framework (REP) [28]. This framework appears to be well-suited for the implementation of our program as it specifies steps needed to maximise fidelity while allowing opportunities for flexibility. REP consists of four phases: pre-conditions (e.g., identifying need, target population, and suitable intervention), pre-implementation (e.g., intervention packaging), implementation (e.g., package dissemination, training, technical assistance, and evaluation), and maintenance and evolution (e.g., preparing the intervention for sustainability). Key components of REP, including intervention packaging, training, technical assistance, and fidelity assessment are crucial to the implementation of effective interventions in health care.

A manual-based training program will be developed by the researchers with assistance of an expert panel consisting of expert nurses, psychiatrists, patients and family members. Nurses in the experimental condition will receive a three-day training program, and psychiatrists and psychologists will receive parts of this training. The trained teams will perform CC during one year. They will be primarily responsible for the coordination and continuity of treatment and care for patients with bipolar disorder. The primary investigator (TV) will supervise the nurses intensively during the performing stage of the intervention, by weekly contact by telephone and regular meetings in the facility with colleagues who also participate in the study. Fidelity will be assessed by means of checklists filled out by the nurses in the experimental group, and by randomly checking the electronic files of patients, by the primary investigator.

Nurses in the control group will be performing Care As Usual, of which the content will be assessed by the researcher at baseline, by means of the checklist mentioned before. The Care consumption will be measured with the TIC-P questionnaire in both groups.

